## Abstract

**Background:**

Oral mucositis (OM) is a common side effect of radiotherapy (RT) that can have severe implications in patients with head and neck cancer (HNC). Traditional Chinese medicine (TCM) formula is widely applied in treating OM, but little substantial evidence exists to clarify it effects. The study intends to determine whether the TCM-based prescription in treating HNC with RT can improve the OM when compared with RT alone.

**Methods:**

A single-center, randomized, two-arm parallel-group, open-label controlled clinical trial will be conducted to determine whether the Zi-Yin-Liang-Ge-San (ZYLGS), which contains *Rx. Scutellariae*, *Rx. Glycyrrhizae*, *Hb. Dendrobii*, *Rx. Ophiopogonis*, and *Hb. Menthae Haplocalycis,* combined with RT can improve the incidence and severity of OM. Two hundred participants will randomly 1:1 to receive at least 6 weeks of RT plus ZYLGS powder or control. The primary outcome measures are onset, gradation of OM (Common Terminology Criteria for Adverse Events v5.0), and oral pain (visual analogue scale). The secondary outcome measures include nutritional status, the EORTC Quality of Life Core Questionnaire and head and neck module. The Patient-Reported Outcomes version of the Common Terminology Criteria for Adverse Events, serious adverse events, and blood and biochemical analysis will be recorded to evaluate the safety. Visits will be performed for each week during the RT treatment period and then 2 weeks in the follow-up period.

**Discussion:**

The study's result will provide a high-level evidence for TCM-based formulation for HNC patients with RT on the effect of OM prevention and management.

## Introduction

1

Oral mucositis (OM) is an iatrogenic condition characterized by erythematous inflammatory changes. It usually manifests on buccal and labial surfaces, on the underside of the tongue, and on the floor of the mouth, as well as on the soft palate of patients receiving radiotherapy (RT) [1]. The severity of OM has a wide range of severities. Some patients develop superficial sore erythema, while others present complete mucosal ulceration in the oral mucosa and pharynx. OM has multiple effects that can compromise the patient's health. Besides causing pain, it can lead to dysphagia, which can reduce nutritional intake. Mucosal ulceration can increase the risk of infection, leading to interruption of cancer treatment. All of these can collectively affect the patient's quality of life (QoL) [2,3]. OM is a frequent adverse event (AE) in patients with head and neck cancer (HNC) treated with RT and/or chemotherapy [4]. This side effect of combination therapy can reduce patients' compliance with treatment, increase the patient's economic burden, and reduce cancer survivorship [5,6]. Timely and adequate intervention for OM is very important.

The main therapeutic goals in treating patients with OM are symptom alleviation and reduction of complications [7]. To achieve these goals, various therapeutic modalities can be employed. Some examples are antioxidants, anti-inflammatory agents, antimicrobials, glutamine, colony-stimulating factors, or low-level laser. However, the efficacy of these approaches is inconsistent in the prevention or treatment of OM [8]. Therefore, adjuvant drugs capable of reducing the incidence of OM and minimizing the associated morbidity of NHC patients should be found.

Chinese herbal medicine (CHM) is a complementary and integrative medicine (CIM) for preventing or treating disease. It is based on medical plants, various minerals, and some animal parts. Having originated in East Asia, it is widely used worldwide [9]. In recent years, many patients with OM have used CHM to prevent or treat RT-induce OM [[10], [11], [12]]. Most CHMs have a “clearing heat” property that can prevent heat toxin accumulated due to RT from gradually consuming the body's energy (*qi*) and body fluid and nutrition (yin) [13], and it has an expected effect in treating OM, according to the theory of traditional Chinese medicine (TCM). The antioxidants in CHM can decrease the production of reactive oxygen species and thereby reduce the severity of mucositis [14]. To date, however, few evidence-based studies on the efficacy of TCM treatment in patients with OM have been conducted.

To explore the potential of CHM formula in preventing OM, we designed a randomized controlled trial study to examine the efficacy of CHM in preventing OM in patients with HNC.

## Methods and analysis

2

### Study design

2.1

This study is a randomized, double-arm, parallel-group, open-label controlled clinical trial conducted at Kaohsiung Chang Gung Memorial Hospital (KCGMH), Taiwan, from August 2021 to April 2023. Patients with HNC scheduled to receive RTO as a component of their cancer treatment will be recruited. The flow chart is shown in Fig. 1. The authors will evaluate the protective effect of a TCM-based prepared medication named Zi-Yin-Liang-Ge-San (ZYLGS), which contains *Rx. Scutellariae*, *Rx. Glycyrrhizae*, *Hb. Dendrobii*, *Rx. Ophiopogonis*, and *Hb. Menthae Haplocalycis*, in preventing and managing OM in patients with HNC receiving postoperative adjuvant or definitive RT or concurrent chemo-radiotherapy therapy (CCRT) as compared with a control group. The methods will remain unchanged throughout the trial. The research protocol has been approved by the Ethics Committee of the KCGMH (202101231A3) and registered at ClinicalTrials.gov (NCT05040425). The Standard Protocol Items: Recommendation for Interventional Trials (SPIRIT) 2013 checklist is provided in **Additional file 1**.

**Fig. 1 fig1:**
[figure not shown]
Study design from enrollment to analysis following the CONSORT 2010 flow diagram.

The study is currently ongoing; the first participant was included on 12 September 2021. We expect to include the last participant in December 2022 and complete the study by April 2023.

### Study participants

2.2

Participants will continue to be recruited from KCGMH via posters and advertisements published on the official hospital website. The recruitment period is expected to last 16 months. Informed consent will be collected from all participants before randomization.

### Eligibility criteria

2.3

#### Inclusion criteria

2.3.1

Participants meeting the following criteria are eligible:1.Patients aged 20–75 years with histologically proven stage II-IV squamous HNC;2.Indication for RT or CCRT;3.No history of antitumor therapies;4.No history of oral ulcer or salivary gland diseases;5.Normal vital signs (body temperature: 36–37.5 °C; heart rate: 60 to 100 beats per minute; respiratory rate: < 20 per minute; mean arterial pressure: 70–100 mmHg), and Eastern Cooperative Oncology Group (ECOG) performance status of 0–2.

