### Randomization and allocation

2.4

By permuted stratified block randomization (block size 4), patients will be randomly assigned to the control group or intervention group in a ratio of 1:1. Stratification factors will include the type of RT (curative/adjuvant) and the application of concurrent chemotherapy (yes/no). A random number generator based on permutation block design will be used to generate randomized sequences for each stratum separately. The random assignment of each participant will be determined before the intervention. To avoid selection bias, the concealed allocation method will use consecutively numbered opaque sealed envelopes.

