### Procedure

2.5

Both groups will receive conventional cancer treatment, including surgery and RT, with or without chemotherapy based on their disease status. All the subjects in the study will receive RT of 6–10 MV photons delivered by a commercialized linear accelerator with the intensity-modulated radiotherapy or volumetric-modulated radiotherapy technique. The radiation protocol (either definitive or postoperative) will be conventional RT, i.e., 5 fractions per week at 60–70 Gy cumulative doses over 6–7 weeks with or without cisplatin (30–50 mg/m^2^ weekly during radiation) as a radio-sensitizer.

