### Assessments

2.7

Each patient will participate in the study for at least 6 weeks, starting from the beginning of RT. Demographic and clinical characteristics recorded at baseline will include gender, age, primary tumor location and stage, scheduled treatment, RT dose, and Karnofsky score. Eligible patients will be randomly assigned to the radiology department for functional assessment and intervention.

The study outcomes will be assessed at baseline (2 weeks pre-RT, t0); at the beginning of RT (t1); at 1 (t2), 2 (t3), 3 (t4), 4 (t5), and 5 (t6) weeks; at the end of RT (t7); and at 2 weeks after completion of RT (t8). The schedule of enrollment is shown in Table 2.

**Table 2 tbl2:** Summary of collected data at each time point according to SPIRIT 2013 guidelines.

Period week	Enrollment	Allocation	Treatment						Follow-up
	Week −2	Week 0	Week 1	Week 2	Week 3	Week 4	Week 5	Week 6	Week 8

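### Primary tumour location, a marker of how much oral mucosa is irradiated, is recorded at baseline but is neither a stratification factor nor a named covariate, so the comparison of arms gives up precision

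*Protocol article*

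**What the plan says.** Inclusion criteria (2.3.1) ask for adults up to 75 years with "histologically proven stage II-IV squamous HNC" and "Indication for RT or CCRT". Neither these nor the exclusion criteria (2.3.2) name a tumour sub-site or require oral mucosa in the treated volume. The Procedure section (2.5) gives "5 fractions per week at 60–70 Gy cumulative doses over 6–7 weeks" without a target volume or oral dose.

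The Introduction says of OM: "It usually manifests on buccal and labial surfaces, on the underside of the tongue, and on the floor of the mouth", and adds the soft palate. It also describes ulceration that reaches the pharynx.

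Assessments (2.7) lists the baseline record as "gender, age, primary tumor location and stage, scheduled treatment, RT dose, and Karnofsky score", so site is in the data. Randomization and allocation (2.4) states: "Stratification factors will include the type of RT (curative/adjuvant) and the application of concurrent chemotherapy (yes/no". Site is not among these factors.

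Data analyses (2.8.2) compares continuous variables with independent-samples t tests and categorical variables with chi-square tests. It uses GEE for trends over time in OM degree and the quality-of-life scales. No covariate is named for any of these.

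**The concern.** All three primary outcomes (onset of OM, its intensity and its pain) depend on mucosa being exposed to radiation. Under criteria this broad, exposure is likely to vary between patients for reasons unrelated to ZYLGS. That variation ends up in the residual spread of an unadjusted comparison. It widens the confidence interval, and a chance excess of low-exposure sites in one arm shifts the estimate.

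A two-sample t test or a chi-square test cannot take account of a baseline variable. The article therefore collects a plausible prognostic factor and then states tests that cannot use it. At stake is the precision and readability of the result, not its validity.

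**Working it through.** **Inputs from the article.** Sample size (2.8.1): difference 0.9, SD 0.7, two-sided level 0.025, power 0.9, 17 per group, 15% dropout, 40 in total. Planned enrolment: 200 in the Abstract, consistent with four DSMB reviews of 50 patients each (2.7.3). At 15% dropout, 200 leaves 100 × 0.85 = 85 evaluable per arm.

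**The plan's own figure.** The noncentrality of the t test at 17 per arm is 0.9 / (0.7 × √(2/17)) = 3.75 on 32 degrees of freedom. Power is 91.3%; 16 per arm gives 89.3%. So 17 per arm is right, and 34 / 0.85 = 40. The stated calculation reproduces.

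**Assumptions, not in the documents.** A share f of patients is at negligible risk and scores 0 in both arms. At-risk patients have mean grade 2.0 (control) and 1.1 (ZYLGS), SD 0.7. Recorded site identifies risk perfectly, which is a best case for adjustment.

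**Precision at f = 20%, 85 per arm.**
- Expected difference: 0.9 × 0.8 = 0.72, with or without adjustment.
- Unadjusted variance, control: 0.8 × 0.49 + 0.2 × 0.8 × 2.0² = 1.032.
- Unadjusted variance, ZYLGS: 0.8 × 0.49 + 0.2 × 0.8 × 1.1² = 0.586.
- Unadjusted SE: √((1.032 + 0.586) / 85) = 0.138 (0.136 in simulation).
- Residual variance with site as an additive covariate: 0.8 × 0.49 + 0.2 × 0.8 × 0.45² = 0.424. The last term arises because the effect is 0.9 in one site group and 0 in the other.
- Adjusted SE: √(2 × 0.424 / 85) = 0.100.

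The same formulas over a range of f:

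| f | Unadjusted SE | Adjusted SE | Variance ratio |
|---|---|---|---|
| 10% | 0.126 | 0.104 | 1.47 |
| 20% | 0.138 | 0.100 | 1.91 |
| 30% | 0.145 | 0.095 | 2.31 |

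**Chance imbalance in site.** The SD of the between-arm difference in site share is √(2f(1−f)/n). At f = 20% it is 0.126 for n = 20 and 0.061 for n = 85. Multiplied by the average at-risk mean of (2.0 + 1.1)/2 = 1.55, a one-SD imbalance moves the difference by about 0.20 and 0.10 grade.

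**Power at two-sided 0.025.** Here 0.9 is taken to apply only to at-risk patients, so the difference is 0.9 × (1−f). The wider SD comes from the variance formula above.

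| f | 17 per arm, SD 0.7 | 17 per arm, wider SD | 85 per arm, wider SD |
|---|---|---|---|
| 0 | 91.3% | 91.3% | >99.9% |
| 10% | 84.1% | 69.8% | >99.9% |
| 20% | 73.9% | 50.0% | 99.8% |
| 30% | 61.0% | 35.6% | 98.1% |
| 40% | 46.8% | 25.4% | 92.0% |
| 50% | 33.0% | 18.2% | 79.8% |

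At 17 per arm with SD 0.7, 90% power needs a difference of 0.881, so the reserve is used up at f ≈ 1 − 0.881/0.9 = 2%. At 85 per arm the needed difference is 0.382, so f can reach about 58% with SD 0.7. With the wider SD, power at 85 per arm still exceeds 90% at f = 40%. If the at-risk control mean were 2.5, it would be 91.6% at f = 30% and 77.8% at f = 40%.

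**The case against.** A reader might infer that patients who cannot develop OM will be enrolled and that the stated 90% power is therefore not delivered. The documents do not support this, for four reasons:
- They give no share of patients whose mouth is spared and do not say that anyone is free of risk. The Introduction says only where OM usually appears, and it mentions the pharynx as well.
- They give no arm means and do not say that the score in the sample size section is a CTCAE grade. The mean of 2.0, which drives the wider SD, is an assumption.
- The 0.9 and 0.7 come from a previous study whose site mix is not described. If that mix was similar, the dilution is already in those figures.
- The power loss arises at 17 per arm. At the planned 200 it needs very heavy dilution.

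A reader might also want to restrict eligibility by treated volume. That would be a change during recruitment, against the Study design section, which says the methods will stay as they are. It would also split the trial into two populations. It is not supported here.

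It is fair to add that randomisation removes bias on average, that the test's error rate already allows for chance imbalance, and that a crude split by site will recover less than the best case above. An analysis plan that is not shown may name covariates. That limits the point to what the article states. It does not remove the point, because the article names its between-group tests and those named cannot adjust.

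**Conclusion.** The point holds as one of efficiency and interpretation. Eligibility is broad in tumour site, site is recorded, and neither the stratification nor the stated tests use it.

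Under the stated assumptions (f = 20%, best-case identification), adjustment cuts the SE at 85 per arm from about 0.14 to 0.10. That is a variance ratio of about 1.9, with a range of 1.5 to 2.3 for f from 10% to 30%. If site carries little information on OM risk, the gain is small and the loss from adjusting is negligible.

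Power at 17 per arm would fall below 90% only if low-risk patients are enrolled and the source study had none. With 200 enrolled, power stays above 90% under substantial dilution. No shortfall in power and no bias is shown.

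**What to change.** In Data analyses (2.8.2), prespecify primary tumour location (oral cavity/oropharynx versus other) as a covariate in the between-group models for OM grade, onset and pain, alongside the two stratification factors. Use regression or GEE in place of the unadjusted t and chi-square tests for these outcomes. Leave eligibility and randomisation as they are.

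The cost is small: the variable is already collected, no visit or procedure is added, and a few degrees of freedom are spent. The grouping of sites and the model should be fixed before outcomes are compared by arm, because the trial is open-label and already recruiting. For onset, if the model reports an odds or hazard ratio, the text should say that the adjusted estimate is conditional on the covariates and need not equal the unadjusted one.

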#### Exclusion criteria

2.3.2

The exclusion criteria are as follows:1.Terminal cancer for which aggressive treatments are unsuitable;2.Impaired renal or hepatic function at initial diagnosis (including chronic kidney disease stages III–V and Aspartate transaminase (AST), Alanine aminotransferase (ALT) ≥ 5 × the upper normal limit);3.Uncontrolled psychiatric problems or altered mental status;4.Previous receipt of medications for other clinical trials.

#### Subject withdrawal criteria

2.3.3

Subjects will be able to voluntarily withdraw from the study at any time. Upon removal of a subject from the study, laboratory and clinical evaluations that would otherwise have been obtained upon completion of the study will be obtained where possible. In the case of subjects removed due to an AE, the patients will continue to receive medical care and remain under observation by the attending physician for as long as deemed appropriate.

### Randomization and allocation

2.4

By permuted stratified block randomization (block size 4), patients will be randomly assigned to the control group or intervention group in a ratio of 1:1. Stratification factors will include the type of RT (curative/adjuvant) and the application of concurrent chemotherapy (yes/no). A random number generator based on permutation block design will be used to generate randomized sequences for each stratum separately. The random assignment of each participant will be determined before the intervention. To avoid selection bias, the concealed allocation method will use consecutively numbered opaque sealed envelopes.

### Procedure

2.5

Both groups will receive conventional cancer treatment, including surgery and RT, with or without chemotherapy based on their disease status. All the subjects in the study will receive RT of 6–10 MV photons delivered by a commercialized linear accelerator with the intensity-modulated radiotherapy or volumetric-modulated radiotherapy technique. The radiation protocol (either definitive or postoperative) will be conventional RT, i.e., 5 fractions per week at 60–70 Gy cumulative doses over 6–7 weeks with or without cisplatin (30–50 mg/m^2^ weekly during radiation) as a radio-sensitizer.

### Interventions

2.6

The TCM preparation consists of concentrated extract powders manufactured by certified pharmaceutical companies. ZYLGS is recommended by the National Research Institute of Chinese Medicine, Ministry of Health and Welfare, Taiwan, for the treatment of a syndrome with impairment of *qi*/yin by excessive heat, which is characterized by OM during RT. The constituents, proportions, actions, and possible side effects in the Taiwan Herbal Pharmacopeia [15] of each CHM regimen are listed in Table 1. The participants will be instructed to take ZYLGS in doses of 4 g (per bag) each time, thrice daily, from the first day of RT until the completion of RT. All of the drugs will be uniformly packed and stored in a Chinese Medicine pharmacy. For administration, 4 g of the formula will be put into the same container with 100 mL of warm water until the particles are completely dissolved, and then an appropriate amount of water will be added for dilution. Participants in the non-TCM treatment group will receive standard oral care for OM based on the Mucositis Research Group of the Multinational Cancer Support Therapy Association and the International Society of Oral Oncology (MASCC/ISOO). Such care mainly includes brushing with a soft toothbrush, flossing and the use of non-medicated rinses [16].

**Table 1 tbl1:** Constituents of TCM preparation and their possible side effects.

Pharmaceutical Latin	Pin Yin	Dosage (g/d)	Actions	Possible side effects
*Rx. Scutellariae*	Huang Qin	2	Drains Fire, clears Heat, dries Dampness, detoxifies and clears Lung and Liver Heat.	Gastric discomfort, nausea and vomiting, diuresis
*Rx. Glycyrrhizae*	Gan Cao	2	Moistens the Lungs, resolves Phlegm, stops cough, clears Heat and relieves Fire toxicity.	Edema, high blood pressure, hypokalemia, and arrhythmia
*Hb. Dendrobii*	Shi Hu	3	Nourishes the Yin, clears Heat, generates fluids, enriches Kidney Yin, reduces Heat from Deficiency and nourishes Stomach and Lung Yin.	Allergic dermatitis, seizure
*Rx. Ophiopogonis*	Mai Men Dong	3	Moistens the Lungs, nourishes the Yin, stops cough, nourishes Stomach Yin, generates fluids and moistens the Intestines.	Allergy, palpitation, nausea and vomiting, flatulence, belching, diarrhea
*Hb. Menthae Haplocalycis*	Bo He	2	Disperses Wind-Heat, cools and clears the head and neck, benefits the throat	Heartburn, headache

As noted, patients in the experimental group will be administered medicine in the TCM clinic and receive the TCM preparation from the first week of RT through the end of RT, or for at least 6 weeks during RT. Taking less than 70% of the study medication during the trial period will be considered non-compliance, and patients meeting this criterion will be excluded from the trial. Patients will be evaluated in the oncology and radiotherapy departments every day (except on weekends) for evaluation of mucositis, oral pain, and lesion. Such assessment is possible due to chemotherapy and RT treatment schedule. Patients will record in a diary the manner of the CHM formula administration, schedules, concomitant use with other medications and reports of adverse effects.

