#### Primary outcome

2.7.1

The primary outcome used in this study will be the onset of OM, intensity of OM and pain. After the start of RT, the patients will be examined daily until onset of OM. Once OM presents, the onset will be recorded in the proforma, and thereafter the degree will be examined weekly until RT is completed and then at 2-weeks post-RT by oncologists.

Subjective assessment of mucositis pain will be performed with a 100-mm visual analog scale (VAS, where 0 = no pain and 100 = worst possible pain) [17], and objective OM grading will be conducted according to the Common Terminology Criteria for Adverse Events, version 5.0 (CTCAE v5.0). The CTCAE v5.0 grades of OM are defined as follows: grade 0, no mucositis; grade 1, asymptomatic or mild symptoms with no intervention indicated; grade 2, moderate pain that does not interfere with oral intake or cause diet adjustment; grade 3, severe pain that interferes with oral administration; grade 4, indication of life-threatening consequences and emergency intervention; and grade 5, death [18].

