#### Safety assessments

2.7.3

No serious AEs are anticipated as a result of the study, and the clinicians will monitor the risks. In cases of AEs caused by anti-cancer treatment or CHM intervention, we will promptly handle the AEs or withdraw the participant from the study. A series of measures to evaluate the safety of the ZYLGS will be monitored throughout the entire trial due to possible herb-induced toxicity. The participants’ blood, liver and kidney function, body weight, and vital signs will be monitored weekly during the treatment period. AEs will be categorized according to the Patient-Reported Outcomes version of the Common Terminology Criteria for Adverse Events (PRO-CTCAE ITEMS Version 1.0) [21] and recorded throughout the study.

For monitoring of the AEs or serious AEs, an independent Data and Safety Monitoring Board (DSMB) review will be conducted for every 50 patients participating in the trial, for a total of four DSMB meetings. A comparative analysis of the incidence of AEs based on the intervention group will be performed at each DSMB review. The DSMB will make recommendations to the research team on appropriate action plans to resolve research safety issues that may arise during the trial. Only when it is determined that an intervention is absolutely necessary for further management of the participants, such as in the event of SAEs, will the research team be un-blinded.

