#### Data analyses

2.8.2

All statistical analyses will be performed by qualified statisticians in SPSS software (SPSS Inc., Chicago, IL, USA; version 13.0) based on the intention to treat (ITT) principle. The data will also be collected and analyzed according to said principle. Continuous variables will be expressed as mean ± SD and compared using unpaired independent *t* tests. Chi-square tests will be used to compare the categorical data between groups.

A two-sided *p* < 0.05 will be considered significant. The trends of change over time in degree of OM, each scale/item of the EORTC QLQ-H&N35 and EORTC QLQ-C30, will be compared between groups with the generalized estimating equation (GEE) in SAS software version 9.4.

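### The 70% intake rule excludes patients after randomisation, can reach the ZYLGS arm only, and contradicts the stated intention-to-treat analysis

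*Protocol article*

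**What the plan says.** Section 2.6 (Interventions) sets the rule: "Taking less than 70% of the study medication during the trial period will be considered non-compliance, and patients meeting this criterion will be excluded". The words that follow make it an exclusion from the trial, not from a named analysis set.

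Section 2.8.2 (Data analyses) says the analyses are "based on the intention to treat (ITT) principle" and adds: "The data will also be collected and analyzed according to said principle".

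On who takes study medication, section 2.6 says that "patients in the experimental group will be administered medicine in the TCM clinic and receive the TCM preparation", whereas "Participants in the non-TCM treatment group will receive standard oral care for OM". Section 2.1 describes the trial as open-label, and no placebo is mentioned.

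Section 2.3.3 (Subject withdrawal criteria) covers subjects removed from the study. The evaluations due at completion are to be obtained where possible, and those removed for an adverse event stay under observation. It does not say that removed subjects are analysed, or that their weekly OM and pain assessments continue.

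**The concern.** Intention to treat keeps every randomised patient in the assigned arm whatever they took. The 70% rule takes patients out because of what they took. A team following section 2.6 will analyse a different population from a team following section 2.8.2, and the article does not say which prevails.

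The rule is also asymmetric. A control patient has no study medication to under-take and so cannot fail it. Any exclusions come from the ZYLGS arm alone, and the balance created by randomisation is lost on one side.

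The exclusions could be related to the primary outcome. ZYLGS is dissolved in water and drunk three times a day. The Introduction says that OM causes pain and can lead to dysphagia, and section 2.7.1 describes "grade 3, severe pain that interferes with oral administration". If patients with worse OM tend to fall below 70%, removing them lowers the mean grade and pain in the ZYLGS arm even if the product does nothing.

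**Working it through.** **Do the texts conflict?** Section 2.4 fixes the assignment before the intervention starts. Intake over the trial period can be known only later, so the rule is a post-randomisation exclusion. No per-protocol set is named to which it could be confined. Section 2.3.3 secures end-of-study evaluations where possible, but neither the weekly grades nor inclusion in the analysis. The conflict therefore stands on the text, without any calculation.

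**Inputs from the plan.** Section 2.8.1 uses a difference of 0.9, SD 0.7, two-sided 0.025 and power 0.9. An exact t-test calculation gives 17 per group (power 0.913; 16 per group gives 0.893), which matches the stated 34. Then 34 / 0.85 = 40, as stated. The SD is taken from here. Section 2.8.1 implies 20 per arm and the Abstract implies 100 per arm (200 in total), so both sizes are shown. The test level is two-sided 0.05 (section 2.8.2).

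**Assumed inputs.** The documents give neither a non-compliance rate nor its relation to severity. Assumed: a fraction p of 10% to 30% of the ZYLGS arm excluded, and a correlation ρ of 0 to 0.7 between severity and a latent tendency to low intake. The 15% dropout in section 2.8.1 is the only attrition figure in the article. It is not a non-compliance rate and serves here only as a reference point.

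**Spurious difference with no true effect.** Shift = ρ × SD × φ(z) / (1 − p), with z the normal quantile at 1 − p.

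- p = 0.15, ρ = 0.5: z = 1.036, φ(z) = 0.2332; 0.5 × 0.7 × 0.2332 / 0.85 = 0.096 grade.
- p = 0.30, ρ = 0.7: z = 0.524, φ(z) = 0.3477; 0.7 × 0.7 × 0.3477 / 0.70 = 0.243 grade.
- ρ = 0: 0 for any p.

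**Error rate.** Simulated trials (20,000 to 40,000 per cell): normal outcomes, no true effect, the fraction p of the ZYLGS arm with the highest latent non-compliance removed, t test at two-sided 0.05.

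| Excluded | ρ | Shift (grade) | Error, 20 per arm | Error, 100 per arm |
|---|---|---|---|---|
| 10–30% | 0 | 0 | about 5% | about 5% |
| 10% | 0.3 | 0.04 | about 5% | about 7% |
| 15% | 0.3 | 0.06 | about 6% | about 9% |
| 15% | 0.5 | 0.10 | about 7% | about 16% |
| 20% | 0.5 | 0.12 | about 8% | about 22% |
| 20% | 0.7 | 0.17 | about 11% | about 40% |
| 30% | 0.7 | 0.24 | about 16% | about 63% |

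The formula is for large samples; at 20 per arm the simulated shifts are slightly smaller (0.09 in the 15%, 0.5 row). Analysing everyone randomised keeps the error at about 5% throughout.

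**The case against.** The best defence is that section 2.8.2 governs the analysis and that the 70% sentence, placed under Interventions, only ends study treatment. Section 2.3.3 shows some intent to keep collecting data after removal, and an analysis plan that is not shown may define the sets. That reading is possible, but the article does not state it: it says exclusion from the trial. This softens the likely consequence without removing the contradiction.

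The direction of bias is also open to challenge, and this part of the defence stands. The rule is cumulative: a patient with full intake at first could stop altogether after 0.70 × 6 = 4.2 weeks (or 0.70 × 7 = 4.9 weeks) and still reach 70%. Severe OM that appears late need not trigger exclusion. Taste, burden or side effects could drive low intake instead. If patients with mild OM were the ones who stopped, the bias would run against ZYLGS.

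A reader might infer three stronger things that the documents do not support:

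- That the patients with the worst OM will certainly be the ones removed. No data on intake by severity are given.
- That the adverse-event provision in section 2.7.3 ("we will promptly handle the AEs or withdraw the participant from the study") is part of the same one-arm problem. It covers events from anti-cancer treatment as well as from the herbal product, so it can apply in either arm, and withdrawal is one of two options.
- That the worst tolerability cases vanish from the safety comparison. Adverse events are recorded throughout the study, patients removed for them remain under observation, and nothing says that earlier events are deleted.

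**Conclusion.** The contradiction between sections 2.6 and 2.8.2 is real, and so is the one-arm reach of the rule. Both follow from the text and the design. Bias toward ZYLGS is plausible but inferred.

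Its size depends on two assumed inputs. Over the range examined, the spurious benefit is 0 to 0.24 grade. The two-sided 5% error is about 5% to 16% at 20 per arm and about 5% to 63% at 100 per arm. The top of each range needs both the heaviest exclusion and the strongest correlation. With 10% to 15% excluded and a correlation of 0.3 or less, the error at 20 per arm stays at about 5% to 6%. Even the largest shift is about 27% of the planned difference (0.24 / 0.9).

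The point still needs correcting before analysis, because it decides who enters the primary comparison. Allowing for 15% dropout protects power but does not protect against selective loss from one arm.

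**What to change.** State in sections 2.6 and 2.8.2 that all randomised patients are analysed in their assigned arm, and that scheduled OM, pain, quality-of-life and safety assessments continue to t8 regardless of intake unless consent is withdrawn. Use the 70% threshold only to define a secondary per-protocol sensitivity analysis.

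Reconcile sections 2.3.3, 2.6, 2.7.3 and 2.8.2 on what removal from the study means for follow-up and for analysis. Decisions on stopping study medication remain with the clinicians and are not part of this change.

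The cost is wording. The sample size is unchanged, and because section 2.6 already has patients evaluated every weekday during radiotherapy, following those with low intake adds little work. The downside is that the estimated effect may be smaller, since patients who took little ZYLGS stay in its arm.
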